**Methods:**

Brain Health Now cohort participants with cognitive difficulties or are not aging successfully are eligible. All participants will be given health resources, a health coach, a goal-setting digital application, and access to an online goal-setting workshop. The intervention group will participate in nine 2-h goal management training sessions and then will enter the healthy lifestyle program. Control participants will enter the healthy lifestyle program directly. A total sample of 100 participants will participate for 12 months. The main outcome is adherence to the healthy lifestyle program, defined as the number of weeks where physical activity adherence targets were met (150 min per week, measured with an activity monitor). Weekly social activities will be captured via self-report with confidential photo validation. We will send weekly health state reports to the participants. Downstream outcomes include cognitive ability, health-related quality of life, mobility, vascular risk profile, and social network size. We will analyze the data using a linear regression model.

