Goal management training (GMT) has become a recommended cognitive rehabilitation strategy to improve executive function among older adults [27]. GMT is a standardized program delivered over 9 weeks in small groups that targets executive dysfunction by teaching goal-directed behaviour, self-management, and mindfulness [28]. GMT also trains participants to use explicit strategies to reduce cognitive load in everyday tasks, and methods to cue attention to maintain focus on specific tasks, through weekly 2 h sessions and home practice. A systematic review and meta-analysis of 15 studies determined that GMT had a small to moderate effect on executive function immediately following the intervention (Hedges’ *g* = 0.227) and at follow-up (Hedges’ *g* = 0.549) among healthy individuals and those with conditions affecting cognitive performance [27].

GMT has been tested very little among people living with HIV. A study of 90 people living with HIV who were randomized to a single session of GMT, GMT plus metacognitive training, or control (education and origami task) found moderate effects of the combined GMT groups on everyday multitasking performance and metacognitive tasks compared to controls [29]. GMT has not been used to augment goal-directed lifestyle changes among people living with HIV.

This study will test an innovative approach to enhance adherence to lifestyle interventions, building on feasibility evidence from pilot trials in the Brain Health Now cohort study, where we have tested three brain-health-promoting interventions, including computerized cognitive training, GMT, and exercise. Feasibility was demonstrated for both GMT and exercise, based on the success of recruitment and retention, improvements in brain health outcomes, and participant feedback [30, 31]. The varied adherence observed in these pilot trials suggests that people living with HIV who have cognitive difficulties may need more assistance to make and sustain behaviour changes. While GMT was developed to improve goal-directed behaviour in general, we recognized that this cognitive rehabilitation approach could be applied to improve the ability to achieve health-promoting lifestyle goals in particular. We therefore hypothesize that GMT priming before a personalized healthy lifestyle program (HLP) will improve adherence to the program and subsequently improve health outcomes, compared to the HLP without GMT priming in people living with HIV experiencing cognitive difficulties.

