### Goal management training

The intervention group will participate in GMT, a standardized cognitive rehabilitation program, which will be provided per the manual. It consists of 9 online sessions, once per week, for two hours [41]. Participants will be given homework to complete between the sessions. There are five steps in GMT [28]. In stage 1, participants are asked to stop and ask what task they are trying to accomplish. They select their goals in stage 2, and these goals are partitioned into smaller steps in stage 3. Stage 4 involves encoding and retention of goals and steps. In stage 5, participants monitor their outcomes to make sure they align with their original goals [28].

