### Confirmatory outcomes

The main confirmatory outcome will be physical activity and social activity adherence to the HLP, hypothesized to be greater with GMT priming. The former will be measured by counting the number of weeks that physical activity adherence targets were met, i.e. 150 min per week of moderate to vigorous exercise, accumulated in bouts of at least 10 min [42]. This outcome will be assessed continuously with the activity monitor (*Garmin VivoFit 4)*. The latter adherence outcome will be the number of documented social activities per week captured through self-report with confidential photo validation. For example, if they attend a yoga class or a painting class, they can take a picture of the yoga studio or art studio and send to a secure email address. A research team member will record the details of the activity and then the picture will be deleted. Participants will be instructed to not take pictures of other people and are not obliged to appear in the picture.

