### Statistical analysis

The analysis assumes that the distribution of physical activity-weeks at the end of the study period will be near normal, permitting a linear regression model; if not, a Poisson model can be used. Both intention-to-treat, with imputation and sensitivity analyses, and per protocol analyses will be conducted. Intention-to-treat will address the benefit of offering GMT as a service to all with need, while the per protocol analysis will address the benefit to those who are able to adhere to the program and will help identify characteristics (including sex and gender) of those most able to benefit. We will follow the Sex and Gender Equity in Research (SAGER) [66] guidelines and will present study data disaggregated by sex and gender. To address bias resulting from missing data, we will conduct multiple imputation on the data for outcomes with sufficient data [67].

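### The per-protocol analysis is aimed at those able to adhere to the program, but adherence to the program is the primary outcome; on either reading of program the comparison does not give the benefit of GMT

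*Protocol article*

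**What the plan says.** The Statistical analysis section of the protocol article plans both intention-to-treat and per-protocol analyses and gives each its own interpretation. For the first, "Intention-to-treat will address the benefit of offering GMT as a service to all with need". For the second, "the per protocol analysis will address the benefit to those who are able to adhere to the program", and it "will help identify characteristics (including sex and gender) of those most able to benefit".

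Three other places show what adherence to the program means in this trial:

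- Abstract, Methods: "The main outcome is adherence to the healthy lifestyle program, defined as the number of weeks where physical activity adherence targets were met".
- Confirmatory outcomes: "The main confirmatory outcome will be physical activity and social activity adherence to the HLP, hypothesized to be greater with GMT priming".
- Background, Lifestyle interventions, where the hypothesis is set out: "GMT priming before a personalized healthy lifestyle program (HLP) will improve adherence to the program".

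The same word is also used for the experimental component. Under Goal management training: "The intervention group will participate in GMT, a standardized cognitive rehabilitation program, which will be provided per the manual".

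The article gives no inclusion rule, threshold or compliance measure for the per-protocol set.

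**The concern.** The phrase that names the primary outcome also describes the people whom the per-protocol analysis is about. Both arms receive the HLP, and GMT is expected to change adherence to it. A set of HLP adherers, if adherence is counted in outcome weeks, is therefore selected on the quantity under test, and a different share of each arm is kept.

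If program means GMT instead, controls have nothing to attend. A filter on attendance then removes people from one arm only, and GMT attenders are set against all controls.

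The last part of the sentence has a separate problem. Describing adherers shows who adheres. Who benefits is a difference between arms that varies with a characteristic, and that contrast loses its randomised basis once retention depends on arm. At stake is a second estimate, reported beside intention-to-treat as the benefit of GMT, that could be too small on one reading and too large on the other.

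**Working it through.** **Inputs from the article (Sample size).** Control mean 9 + 4 = 13 activity-weeks; GMT mean 22 (50% of 43); difference 22 − 13 = 9; SD 11; 50 per arm. The article puts the 9-week difference over 43 weeks, so both means are read as counts out of 43. It gives no per-protocol figure to reproduce.

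**Assumed, not in the article.** The cut-off c that makes someone an adherer; the shape of the distribution; the share of the GMT arm that attends; and the correlation ρ between attendance and activity-weeks.

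**Reading 1: program = HLP, adherer = at least c activity-weeks, both arms filtered.**

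For a normal outcome, the mean among those kept is μ + σ·λ(a), with a = (c − μ)/σ and λ(a) = φ(a)/[1 − Φ(a)].

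Example, c = 13:
- GMT: a = (13 − 22)/11 = −0.818, λ = 0.360, mean = 22 + 11 × 0.360 = 26.0; 79% kept.
- Control: a = 0, λ = 0.798, mean = 13 + 11 × 0.798 = 21.8; 50% kept.
- Difference = 4.2 weeks, against a true 9.

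The count cannot fall below 0 or exceed 43, so the calculation was repeated with a beta-binomial on 43 weeks with the same means and SD.

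| Cut-off c (assumed) | Normal: difference | Beta-binomial: difference | Kept, GMT vs control (beta-binomial) |
|---|---|---|---|
| 9 | 5.1 | 4.0 | 86% vs 56% |
| 13 | 4.2 | 2.9 | 77% vs 44% |
| 22 | 2.6 | 1.4 | 52% vs 23% |

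The true 9-week difference becomes 1.4 to 5.1 weeks. Even the mildest case loses (9 − 5.1)/9 = 43% of it, and the sets kept differ in size and make-up between arms.

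**Reading 2: program = GMT, only the GMT arm filtered, no true effect.**

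If a proportion k attends and attendance correlates ρ with the outcome, the GMT mean rises by ρ·σ·φ(z)/k, where z is the normal point with upper-tail area k.

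- k = 0.8: φ(z)/k = 0.280/0.8 = 0.350. For ρ = 0.3: 0.3 × 11 × 0.350 = 1.2 weeks. For ρ = 0.5: 1.9 weeks.
- k = 0.7: φ(z)/k = 0.348/0.7 = 0.497. For ρ = 0.3: 1.6 weeks. For ρ = 0.5: 2.7 weeks.

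The spurious difference is +1.2 to +2.7 weeks, at most 2.7/9 = 30% of the difference that the trial is sized for. With 40 or 35 attenders against 50 controls, the standard error is 11·√(1/40 + 1/50) = 2.33 or 11·√(1/35 + 1/50) = 2.42. The bias is then about 0.5 to 1.1 standard errors, and a nominal two-sided 5% test rejects about 8% to 20% of the time. If ρ = 0 there is no bias.

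**The case against.** The strongest reply is that the article never states a per-protocol rule. One clause says what the analysis is for, and the set itself is commonly defined in an analysis plan. The first half of the sentence concerns offering GMT, so its natural counterpart is benefit among those who complete GMT, which the article also calls a program. A third reading is open too: engagement with the coach, tracker or app is not the same as reaching the weekly activity target. And a per-protocol set could apply completion criteria to both arms.

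Much of this stands. A reader might infer that the plan does select on its outcome and so cannot estimate benefit at all. The article does not support that as a flat statement: the circular reading follows from its wording but is not the only one, and GMT attendance is plausible. Nor does the circularity extend to the downstream health outcomes, where selection on adherence is selection on a mediator, biased but not circular. A reader might also take the figures above as predictions. They are illustrations: no cut-off, attendance rate or correlation is in the article, and the shrinkage depends on the distribution as well as the cut-off.

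What does not stand is that this is only missing detail. A threshold added later would not repair the stated aim, because under each of the two main readings the comparison is not randomised.

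**Conclusion.** The point holds in conditional form. The article uses one phrase for the primary outcome and for the per-protocol target, and leaves open which program is meant. If the HLP is meant, with adherence counted in activity-weeks or social-weeks, the analysis conditions on the outcome; a true 9-week difference shrinks to about 1.4 to 5 weeks under the plan's means and SD and assumed cut-offs of 9 to 22 weeks. If GMT attendance is meant and only that arm is filtered, a null effect becomes about +1.2 to +2.7 weeks under assumed attendance of 70–80% and correlation 0.3–0.5. Neither result is the benefit of GMT in those able to adhere, and neither shows who benefits. The intention-to-treat analysis is unaffected, so the main conclusion of the trial is not at risk. The exposure lies in the secondary claim placed beside it.

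**What to change.** 1. State which program is meant, and that activity-weeks and social-weeks are never used to define the per-protocol set.
2. Define compliance only by GMT sessions attended, out of the nine, with a threshold fixed before the data are analysed.
3. Estimate the effect in compliers as a complier-average causal effect: all randomised participants kept in both arms, randomisation as the instrument. State its exclusion restriction, that attendance below the threshold has no effect. This is doubtful for a skills course taught over nine sessions, so add a sensitivity analysis that uses the number of sessions attended.
4. Label any conventional per-protocol comparison as supportive and non-randomised.
5. Examine who benefits through interactions of arm with sex, gender and baseline cognition in the intention-to-treat population, labelled exploratory and, with 50 per arm, low-powered.

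The cost is revised wording, a log of GMT attendance, a little more programming, and wider confidence intervals than a naive per-protocol analysis would show. The article describes the study as ongoing, so the change could be made before analysis.

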### Sample size

Sample size calculations were based on estimates of usual rates of adherence to physical activity for Canadian adults estimated at 10–20% of the time [68], translating to approximately 9 of 52 weeks for the control group and a desired 22 weeks (50% of 43 weeks) in the GMT priming group, which is the targeted adherence rate for interventions for cardiovascular risk factor improvement [69]. As we expect that elements of the HLP program will lead to some activity improvement in the control group (+ 4 weeks), we will power our study to detect a minimum difference of 9 activity weeks between groups over 43 weeks with an estimated SD of 11 weeks. With adjustment of the variance (standard deviation) by 15% to account for dropouts and the need to impute data, this yields an effect size of 0.71 [70]. For 90% power and risk of Type I error of 0.05, the required number of people is 38 participants per group. We will therefore target a total sample of 100 (50 per group) to account for uncertainty in our sample size assumptions and incomplete data. This sample size will also be sufficient to permit other statistical models to be used in the case of non-normality, such as ordinal regression.

Taking advantage of the trial being embedded in the cohort, we will also compare platform outcomes for trial participants with platform outcomes for people who were eligible for the trial but not enrolled, including those at other sites, providing information about how the HLP with or without GMT compares to tailored brain health risk recommendations alone.

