*Set*: One of the short video modules will include instruction on specific, measurable, attainable, relevant, and time-bound (SMART) goals and demonstration of the goal-setting app to use for recording and monitoring goals. The app will guide all the participants through the steps to write and follow up on their SMART goals. Participants will be encouraged to be as specific as possible when filling in a box on the app with an aspect of their health that they wish to improve. The goal-setting app will give them feedback on their goals through simplified Goal Attainment Scaling [40]. Participants will have the option to contact other participants with similar goals via their health coach. For example, if multiple participants have goals related to yoga, the coach can suggest they communicate and help each other achieve their goals, as long as the participants have consented to this option.

*Go*: Following the workshop, the participants will be randomized. Randomization will be done in a 1:1 ratio by the study statistician using randomization.com. Stratification by language will be carried out, as GMT will be done in either French of English. The intervention group will participate in GMT for 9 weeks and then will enter the HLP for 43 weeks. Control participants will enter the HLP directly and will participate for 52 weeks. It is not possible to blind participants in this type of study.

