### Outcome measures

Refer to Table 1 for a list of outcome measures that will be administered in this study.

**Table 1 Tab1:** Outcome measures

Outcome	Measure	Value
*Confirmatory outcomes*		
Primary 1: uptake of the recommendations for physical activity	Number of physical activity-weeks. Recorded by Garmin VivoFit 4	Number of weeks in which physical activity guidelines are met (150 min of moderate to vigorous activity in bouts of 10 min) [42]
Primary 2: uptake of the recommendations for social activity	Number of social activity-weeks. Recorded by pictures provided by participants	Number of weeks in which at least one social activity was attended
*Explanatory outcomes*		
Achievement of personal goals	Goal attainment scaling [40, 43] Recorded on the goal-setting app	N and diversity of goals set and met
Physical activity pattern	Daily step counts, time spent in cadence bands for moderate (100 steps/min) and vigorous (130 steps/min) intensity [44], sitting time. Recorded by the Garmin VivoFit 4	Trajectory of weekly cumulative step counts (rising, stable, falling) Trajectory of weekly cumulative sitting time (rising, stable, falling)
General Health perception, sleep, distress, pain, fatigue, depression, anxiety, quality of life	Visual Analogue Health States [45]	0–10 for each
*Downstream health outcomes (platform measures)*		
Mood	RAND-36 Mental Health Inventory [46]	0–100
Energy/fatigue	RAND-36 Vitality [46]	0–100
Physical function	RAND-36 Physical Function Inventory [46] and five-repetition sit-to-stand test [47]	0–100; time in seconds
Performance based-report cognitive ability	Brief Cognitive Ability Measure (B-CAM) [48]	0–35 English / 42 French
Self-report cognitive ability	Communicating Cognitive Concerns Questionnaire (C3Q) [37]	0–36
Health related quality of life	EuroQol Five Dimensions Questionnaire (EQ-5D) [49], Patient Generated Index [50, 51]	0–1; 0–100
Improved vascular risk profile	Framingham Cardiovascular Disease Risk Score [52, 53]	Probability of stroke
Social network size	Social network size and quality [54]	0–100

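### The counting window for activity-weeks is inconsistent: time in the lifestyle program is 52 weeks in controls and 43 in the GMT arm, and the planned 9-week difference subtracts one base from the other

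*Protocol article*

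**What the plan says.** **Time in the program.** Methods, Intervention (the *Go* paragraph) gives the two arms different HLP periods. For the intervention arm: "The intervention group will participate in GMT for 9 weeks and then will enter the HLP for 43 weeks". For the control arm: "Control participants will enter the HLP directly and will participate for 52 weeks".

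**Outcome.** Table 1 gives the value of the first primary outcome as a count: "Number of weeks in which physical activity guidelines are met". The Confirmatory outcomes section ties both primary outcomes to the program, "The main confirmatory outcome will be physical activity and social activity adherence to the HLP", and describes the physical activity outcome as "counting the number of weeks that physical activity adherence targets were met". It adds: "This outcome will be assessed continuously with the activity monitor". Neither place states a start week, an end week or a denominator.

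**Analysis.** The Statistical analysis section plans a linear regression on activity-weeks at the end of the study period, with a Poisson model as fallback.

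**Planning figures.** The Sample size section starts from "approximately 9 of 52 weeks for the control group and a desired 22 weeks (50% of 43 weeks) in the GMT priming group", allows controls 4 more weeks, and powers the trial for "a minimum difference of 9 activity weeks between groups over 43 weeks" with an SD of 11 weeks, inflated by 15%.

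**The concern.** A count of weeks can be compared between arms only if both arms have the same number of weeks in which to score. Here the outcome is described as adherence to the HLP, and the HLP lasts 9 weeks longer in one arm. The one place that names a window, the Sample size section, says 43 weeks but uses a control figure built on 52.

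Three windows are compatible with some part of the text:

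- each arm's own HLP period (52 against 43 weeks);
- a common 43 weeks;
- all 52 weeks from randomisation.

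They do not give the same estimate. Under the first, part of the difference between arms reflects the length of observation and not adherence. Left open, the choice could also be made after the data are known. Social activity-weeks, as Table 1 defines them, have the same problem.

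**Working it through.** **Inputs**

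- HLP time: control 52 weeks, GMT 43 weeks (Intervention, *Go*).
- Control: 9 of 52 weeks, plus 4 (Sample size).
- GMT: 50% of 43 weeks, rounded to 22 (Sample size).
- SD 11, inflated by 15%: 11 x 1.15 = 12.65 (Sample size).
- 50 per group (Sample size). A two-sided 5% test is assumed, because sidedness is not stated.

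**1. The plan's own difference**

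- Control: 9 + 4 = 13, and 13/52 = 25%.
- GMT: 0.50 x 43 = 21.5, rounded to 22.
- 22 - 13 = 9, and 9/12.65 = 0.71.

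The 9 weeks and the effect size of 0.71 both reproduce. The 9 is a 43-week figure minus a 52-week figure.

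**2. The same assumptions on a common 43-week base**

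- Control: 13 x 43/52 = 10.75.
- GMT: 21.5.
- Difference: 21.5 - 10.75 = 10.75 weeks.

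The result varies a little with rounding. With GMT at 22 it is 11.25. If only the base of 9 is rescaled and the +4 kept whole, control is 9 x 43/52 + 4 = 11.44 and the difference from 22 is 10.56.

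**3. If each arm is counted over its own HLP period**

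With the same weekly adherence r in both arms, the expected difference (GMT minus control) is 43r - 52r = -9r.

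| Weekly adherence in both arms | Control, 52 weeks | GMT, 43 weeks | Difference |
|---|---|---|---|
| 17.3% (9/52, the plan's base rate) | 9.0 | 7.4 | -1.6 |
| 25% (13/52, the plan's control rate) | 13.0 | 10.75 | -2.25 |
| 50% (the plan's GMT target, in both arms) | 26.0 | 21.5 | -4.5 |

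**4. Chance of a significant result with no true difference in weekly adherence**

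Two-sample t-test, 50 per group, own-period counting. The nominal rate is 5%. At 25% adherence the standardised artefact is 2.25/11 = 0.205 or 2.25/12.65 = 0.178.

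| Weekly adherence | SD 11 | SD 12.65 |
|---|---|---|
| 25% | 17% | 14% |
| 50% | 53% | 42% |

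**5. Effect on a real benefit**

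Under the plan's rates (25% and 50%), own-period counting gives 21.5 - 13 = 8.5 weeks instead of 10.75. The loss is 2.25/10.75, about 21%.

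**6. Effect on power**

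At 50 per group and SD 12.65, power is about 94% for 9 weeks, 91% for 8.5 and 99% for 10.75. This assumes that the SD does not depend on the window.

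**7. All 52 weeks from randomisation**

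Control stays at 13. The GMT arm scores 21.5 plus 9a, where a is its weekly adherence during the 9 GMT weeks. The article gives no value for a, so it is varied here:

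- a = 0: 21.5 - 13 = 8.5 weeks;
- a = 25%: 23.75 - 13 = 10.75 weeks;
- a = 50%: 26 - 13 = 13 weeks.

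**The case against.** A reader might infer that the primary comparison is biased against GMT as it stands. The documents do not support that as an unconditional statement. The bias exists only if each arm is counted over its own HLP period, and no sentence says that it will be. The Sample size section names 43 weeks for the difference between groups, which points to a common window. Continuous monitoring, and analysis at the end of the study period, would also fit a 52-week count from randomisation. Under that count the 9 weeks before the HLP are a cost of the strategy, which suits the stated intention-to-treat aim. This part of the objection stands. But it does not show that an equal window is planned. The outcome is called adherence to the HLP, and the sample size arithmetic follows the own-period count.

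A reader might also take the 50% row as the likely size of the problem. It needs both arms at the GMT target with no GMT effect, which is not what the plan assumes, so it is only an upper illustration. The 25% row uses the plan's own control rate. Nor can the artefact create a false positive in favour of GMT, since it runs the other way.

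It can be said that an article leaves counting windows and model offsets to the full protocol or analysis plan. That is fair for the Poisson offset, and its absence alone would be no finding. It does not cover a difference labelled as 43 weeks but computed from a 52-week control figure, because that contradiction is in the text.

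Finally, the mixed bases might suggest an underpowered trial. They do not: on the common 43-week base the assumed difference exceeds 9 weeks.

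**Conclusion.** The concern holds as an inconsistency in the counting window, with a conditional bias.

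- **Certain from the text:** HLP time differs by 9 weeks, the outcome is a raw count without a denominator, and the 9-week difference is not a 43-week difference. On 43 weeks the plan's rates give 10.75 (10.56 to 11.25, depending on rounding and on how the +4 is treated).
- **Conditional on own-period counting:** the GMT arm loses 9r weeks. At the plan's 25% control rate that is 2.25 weeks, a quarter of the 9-week target. The chance of a spurious significant result is 14% (SD 12.65) to 17% (SD 11), and the assumed benefit falls from 10.75 to 8.5 weeks. A larger sample would not remove this.
- **Not affected:** the target of 100 participants.

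The window should be fixed before analysis, because it determines what the primary estimate means. The figures rest on a constant weekly rate within each arm, an SD that does not depend on the window, and a two-sided 5% test.

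**What to change.** 1. In Table 1 and Confirmatory outcomes, define both activity-week counts over one window of equal length in both arms. Either weeks 10 to 52 after randomisation (43 weeks in each arm) or all 52 weeks from randomisation is defensible. Name one as primary and use the other as a sensitivity analysis.
2. Alternatively, keep each arm's HLP period and analyse the proportion of weeks on target, or use the number of HLP weeks as an exposure offset if the Poisson model is used.
3. Restate the Sample size inputs on the chosen base. On 43 weeks they are 10.75 (25%) and 21.5 (50%), and 9 weeks can stay as a deliberately conservative minimum difference. On 52 weeks an assumption about activity during the 9 GMT weeks has to be added. There 9 is conservative only if adherence in those weeks exceeds 0.5/9, about 6%.

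**Cost.** Wording in the outcome, analysis and sample size sections. The activity tracker records continuously, so the physical activity count needs no new data. Each window has a drawback. With weeks 10 to 52, the first 9 control weeks leave the primary count and controls have already had 9 weeks of HLP when counting starts. With all 52 weeks, the GMT arm is counted for 9 weeks before its HLP begins, so the estimate describes the whole strategy and not adherence once in the program.

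### The stated requirement of 38 per group does not follow from the stated effect size of 0.71: a two-sided test needs 42 or 43, and 38 gives about 86% power, although the target of 50 still suffices

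*Protocol article*

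**What the plan says.** The calculation is in the protocol article, Methods, Sample size. The trial is powered to "detect a minimum difference of 9 activity weeks between groups over 43 weeks", "with an estimated SD of 11 weeks". The next step is described as follows: "With adjustment of the variance (standard deviation) by 15% to account for dropouts and the need to impute data", and "this yields an effect size of 0.71". The requirement comes directly after: "For 90% power and risk of Type I error of 0.05, the required number of people is 38 participants per group". The section then sets the recruitment target at 100, or 50 per group, and explains the excess by uncertain assumptions and incomplete data.

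Allocation is equal (Methods, Intervention, the Go paragraph: "Randomization will be done in a 1:1 ratio by the study statistician"). The Statistical analysis section names a linear regression on activity-weeks. Neither section says whether the test is one- or two-sided, and the calculation takes no credit for covariates.

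**The concern.** The effect size, power, Type I error and sample size are given in consecutive sentences, and the last should follow from the other three. It does not. The phrase describing the 15% adjustment also treats the variance and the standard deviation as one quantity. Inflating one by 15% is not the same as inflating the other, so a reader cannot tell which calculation was done.

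At stake is the accuracy of the power statement for the physical activity outcome. The target of 50 per group is presented as the requirement plus a reserve. If the requirement is understated, the reserve looks larger than it is.

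**Working it through.** **Inputs** (all from Sample size, except the allocation ratio): difference 9 weeks; SD 11 weeks; adjustment 15%; effect size d = 0.71; power 0.90; Type I error 0.05; required n 38 per group; target 50 per group; allocation 1:1. Two-sided testing is assumed, and one-sided testing is also tried.

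**1. The effect size reproduces if the SD is inflated.**

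11 x 1.15 = 12.65, and 9/12.65 = 0.7115, which rounds to 0.71.

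**2. The requirement does not reproduce from 0.71.**

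Normal approximation: n per group = 2(z₀.₉₇₅ + z₀.₉₀)²/d² = 2(1.960 + 1.2816)²/0.71² = 21.01/0.5041 = 41.7, so 42.

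Two-sample t test (noncentral t): 42.67, so 43. With d = 0.7115 it is 42.50, again 43.

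**3. Power at 38 and at 50 per group.**

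Normal approximation at 38: Φ(0.71 x √(38/2) − 1.960) = Φ(3.095 − 1.960) = Φ(1.135) = 87.2%.

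| n per group | d | Power, normal | Power, t test |
|---|---|---|---|
| 38 | 0.71 | 87.2% | 86.3% |
| 43 | 0.71 | 90.9% | 90.2% |
| 50 | 0.71 | 94.4% | 94.0% |

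**4. Could another reading give 38 from 0.71?**

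- *Rounding.* Values from 0.705 to 0.7149 round to 0.71. Over that range the t test needs 43 to 44 and the normal approximation 42 to 43.
- *One-sided 0.05.* At d = 0.71 the need is 34 (normal) or 35 (t test, 34.67).
- *Effect size implied by 38.* For 90% power with a two-sided test, d would have to be 0.744 (normal) or 0.753 (t test). Neither rounds to 0.71.

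**5. Routes that do reach 38, none of which uses 0.71.**

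- *Variance x 1.15.* SD = 11 x √1.15 = 11.80; d = 9/11.80 = 0.763; t test n = 37.09, so 38.
- *Uninflated SD, then a 15% allowance for dropout.* d = 9/11 = 0.818; normal n = 21.01/0.669 = 31.4, so 32; 32/0.85 = 37.6, so 38.
- *Uninflated SD by t test, then a 15% increase.* n = 32.38, so 33; 33 x 1.15 = 37.95, so 38.

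**6. Excess of the target over the requirement.** The article implies 50 − 38 = 12 per group. With 43 it is 50 − 43 = 7.

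**The case against.** The strongest reply is that nothing the trial does depends on 38. The only recruitment figure acted on is 50 per group, which exceeds 43 and gives 94% power at the stated effect size. No recruitment or stopping rule is tied to 38, and the article never states a reserve of 12; that figure comes from subtraction. The target was also set above the requirement to absorb errors in the assumptions, and this discrepancy is well within that allowance. All of this stands. It limits the consequence but does not make 38 correct.

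On sidedness, the article is silent. Under a one-sided test 38 would give about 92% power, so it would suffice, but it would still not be the required number.

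Three stronger readings are tempting, and the article supports none of them.

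- *The trial loses its 90% power if dropout leaves 38 analysable per group.* A reader might infer this, particularly as the Background cites withdrawal of 20–29% in exercise trials in this population. But the 15% inflation is stated to cover dropout and imputation, so 0.71 already carries that penalty. Applying 0.71 to completers counts the loss twice. On the article's own figures, 38 completers per group with SD 11 have d = 0.818 and about 94% power (t test, 94.1%).
- *The error arose because the variance was inflated for one figure and the SD for the other.* The wording invites this, but step 5 shows other routes to 38. The article shows no working and relies on a reference that is not at hand. Only the mismatch is established.
- *The effect size should be restated as 0.76 and 38 kept.* That is right only if the variance was in fact inflated. If 38 came from a dropout allowance on the uninflated calculation, 0.76 would be a new error.

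**Conclusion.** The point holds as an internal inconsistency in the power statement. With the effect size of 0.71, a two-sided test at 0.05, equal groups and no gain from covariates, 90% power requires 42 per group (normal) or 43 (t test), not 38. The shortfall is 4 to 5 per group, and 38 gives about 86% power. The 86% refers to 38 per group under the already inflated SD, not to 38 completers.

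The trial is not shown to be underpowered: the target of 50 per group gives about 94%. What changes is one stated figure and the reserve it implies, which is about 7 per group instead of 12. Confidence is high in the mismatch. The source of 38 remains unknown.

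**What to change.** State which quantity the 15% was applied to (the SD, the variance or the sample size) and make the effect size and the requirement follow from that one choice. State also whether the test is one- or two-sided.

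If the SD was inflated, as 0.71 implies, and the test is two-sided: write that the SD rises from 11 to 12.65, keep 0.71, replace 38 with 43 per group, and add that 50 per group gives about 94% power. If another route was used, the effect size must be restated to match it; only the authors can say which.

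The cost is a few words and one or two figures in the Sample size section. The reserve will look smaller, but no participants are added.
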